Oculomotor	eye movements, binocular cooperation	strabismus, convergence insufficiency, 3rd, 4th and 6th nerve palsies, nystagmus, gaze abnormality	9: Quick movements are hard to follow with my eyes. 10: I have double vision. 11: I can read better with one eye closed. 12: I have trouble with depth perception. I find it hard to say which one of two objects is closer.
Optic nerve	optic nerve disease	opticopathy, glaucoma (Mimics: structural lesion, hemianopsia)	13: Colours seem to be paler than before. 14: I can’t read plain text on a coloured or grey background. 15: I run into objects or people or feel that parts of my visual field are missing. 16. I have problems with rapid changes of light intensity. (For example, driving through a tunnel).

The Visual Impairment in Parkinson’s Questionnaire (VIPD-Q) has been divided in 4 domains as shown above. These domains were agreed upon by a consensus procedure involving three independent ophthalmologists (one from each study site). Six questions of the questionnaire could not be categorized in one domain, but rather indicate the involvement of more than one anatomical domain

The VIPD-Q is both available on paper and online (in English, German and Dutch). We will distribute the questionnaire using different strategies: (1) PD patients visiting the neurologic outpatient clinics at the three study sites (complete the questionnaire on site); (2) PD patients receiving care in one of the participating centres (will receive the questionnaire via post); and (3) PD patients interested in research, having registered on a platform for research and innovation in PD: www.parkinsonnext.nl (will receive the online questionnaire through e-mail). Healthy controls will be recruited by asking partners and family members of participating patients to also complete the questionnaire.

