### Phase 2: neurological and ophthalmological assessment

#### Patient collective and recruitment

From the responders of phase 1, a sample of 100 patients will be invited for a full clinical and ophthalmological assessment. Patients will be selected based on their scores on the VIPD-Q aiming to include 70 patients with and 30 patients without visual impairment, which is operationally defined as patients scoring the highest 30% or the lowest 30% on the screening questionnaire, respectively. Due to personnel capacity, a sample of 30 patients in the Netherlands (10 in the lowest 30% and 20 in the highest 30%) and 70 patients in Austria (20 in the lowest 30% and 50 in the highest 30%) will be selected and invited for the clinical and ophthalmological assessment. The OLVG hospital only participated in phase 1 of this study. Inclusion and exclusion criteria are described in Table 2. Selection will start after at least 250 questionnaires have been completed. (See Fig. 1).

**Table 2 Tab2:** Inclusion and exclusion criteria

Inclusion criteria	Exclusion criteria
Diagnosis of PD according to the UKPDSBB criteria	Hoehn and Yahr Parkinson’s staging score ≥ 4
The patient must be able and willing to give written informed consent	Secondary cause of parkinsonism as detected by history (e.g. drug-induced parkinsonism)
The patient must be willing to participate in all study related activities and visits	Secondary cause of parkinsonism as detected by investigation (e.g. vascular parkinsonism as detected by neuroimaging)
Age of onset Parkinson’s disease > 30 years	Dementia according to DSM-IV
Stable doses of Parkinson medications ≥4 weeks	Major depressive disorder according to DSM-IV
Current age ≥ 60 years	Psychotic disorder(s) according to DSM-IV
	Prior brain surgery (except deep brain stimulation)
	Previous eye surgery (except phacoemulsification for cataract and artificial lenses)
	Blindness in 1 eye
	Medication that influences normal visual function other than PD medication. (Detailed information, please see Additional file 2: Appendix 2)
	Systemic diseases that may cause eye problems (HIV, DM type I, type II if the patient had ophthalmologic therapy and/or abnormalities at last screening)
	Neurodegenerative diseases other than Parkinson’s disease
	History of lesions near the optic chiasm or occipital cortex
	Migraine

Inclusion and exclusion criteria of the Visual Impairment in Parkinson’s Disease study

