
### Statistical analysis plan

95% Confidence intervals, means, standard deviations and frequency distributions will be calculated for all outcomes. Nonparametric variables (age, disease duration, LED, total score VIPD-Q) will be expressed as the median, interquartile range (IQR), minimum, and maximum. To compare groups, we will use the student’s t-test for parametric continuous variables and the Mann-Whitney U test for non-parametric continuous variables. All analyses will be performed with SPSS 22.0 (SPSS Inc., IBM, Chicago, IL, USA).

To address the first study objective (validity of the screening questionnaire), we will compare the results of the VIPD-Q with the ophthalmological assessments using analysis of intraclass correlation coefficient (ICC), with Cohen’s kappa. The results of the ophthalmological assessments will be categorized in visual disorders within the domains of the VIPD-Q (ocular surface, intra- ocular, oculomotor and optic nerve). We hypothesize moderate to good correlation (ICC > 0.5) between the scores on the domains based on the ophthalmological tests and the scores on the domains based on the screening questionnaire. We will also address correlation for the total score. In addition, we will calculate optimal cut-off points of the domains and total score of the VIPD-Q using the receiver operating characteristic (ROC).

For the second and third objective (determine the prevalence and severity of visual problems in PD; impact on clinical functioning), PD patients will be compared with healthy controls using chi-square-tests for categorical values (sex, education, co morbidity, visited ophthalmologist, visual aid, vision changes during the day, difficulties with daily activities, impact on quality of life) or Mann-Whitney U test for non-parametric continuous variables (age, total score VIPD-Q, score per domain). Furthermore, the relationship between falling, disease duration, MDS-UPDRS, hand-eye dexterity, gait and balance tests, and visual problems will be assessed using multiple linear regression analysis.

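### Minor: phase 2 is recruited to fixed country quotas, but none of the named analyses carries a country term, so pooled associations and the pooled cut-off can absorb differences between the two examining centres

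*Protocol article*

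**What the plan says.** All references are to the protocol article.

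- **Phase 2, Patient collective and recruitment.** The section states that "a sample of 100 patients will be invited for a full clinical and ophthalmological assessment", "aiming to include 70 patients with and 30 patients without visual impairment". The split by country is given as "a sample of 30 patients in the Netherlands (10 in the lowest 30% and 20 in the highest 30%) and 70 patients in Austria", with the Austrian part made up of 20 low and 50 high scorers. The reason given is operational: "Due to personnel capacity". Also, "The OLVG hospital only participated in phase 1 of this study", which leaves one examining centre in each country (Nijmegen and Innsbruck). The section does not say whether the 30% limits are set over all responders or within country.
- **Phase 1: screening questionnaire.** "The VIPD-Q is both available on paper and online (in English, German and Dutch"). The article does not say which version any phase 2 patient completes.
- **Statistical analysis plan.** For objective 1 it names ICC with Cohen's kappa, and adds that "we will calculate optimal cut-off points of the domains and total score of the VIPD-Q using the receiver operating characteristic (ROC"). For objective 3 it names a multiple linear regression relating falls, duration and severity of disease, dexterity, and gait and balance to visual problems. Country, centre and language are not mentioned in any of these.
- **Ophthalmological assessment.** Reading speed is scored in words per minute. Visual fields may be measured on either a Humphrey or an Octopus device, and the article does not say which centre uses which.

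**The concern.** Country is a sampling stratum in phase 2, and it carries other things with it: the examining team, possibly the perimeter, and very probably the language of the questionnaire. It can therefore influence both the VIPD-Q score and the examination against which that score is validated.

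Two results are exposed. First, if the two centres differ on both a visual measure and a gait or balance measure, a regression without country shows an association between the two that reflects only where the patient was examined. Second, if scores at the same eye status differ between centres, a single cut-off has a different sensitivity and specificity in each country, and the pooled pair describes neither. With 70 of 100 patients from Austria, the pooled figures would lie closer to the Austrian ones.

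**Working it through.** **1. The plan's own figures.** Netherlands 10 + 20 = 30; Austria 20 + 50 = 70. Low 10 + 20 = 30; high 20 + 50 = 70. The total is 100, so the quotas are consistent.

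**2. Do the quotas confound score group with country?** The share of high scorers is 20/30 = 66.7% in the Netherlands and 50/70 = 71.4% in Austria. The odds ratio is (50 × 10)/(20 × 20) = 1.25 and phi is 0.05 in absolute value. A country difference of D standard deviations in an outcome shifts the crude high-versus-low contrast by D × (50/70 − 20/30) = 0.048 D, which is 0.02 SD for D = 0.5 and 0.05 SD for D = 1. This is negligible.

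**3. Can country create an association between two measured variables?** Step 2 does not cover this, because the regression uses measured visual and motor variables, not the score group. Assume that the centres differ by d within-centre SDs in the same direction on both measures, and that the measures are unrelated within centre. With p = 0.3 in the Netherlands, p(1 − p) = 0.21 and

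r = 0.21 d² / (1 + 0.21 d²)

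- d = 0.5: 0.0525/1.0525 = 0.05
- d = 1.0: 0.21/1.21 = 0.17

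The standard error of a correlation near zero with n = 100 is about 1/√99 = 0.10. The lower value is half a standard error and the upper one about 1.7. The article gives no estimate of d.

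**4. How would a pooled cut-off behave?** Assumptions: equal-variance normal scores; a cut-off giving 0.80/0.80 if there is no shift, so the separation is 2 × 0.842 = 1.683 SD (AUC about 0.88); Dutch scores lower by s at the same eye status; the quota cells standing in for cases and non-cases (Netherlands 20/10, Austria 50/20); the cut-off c maximising the pooled Youden index. On a scale where Austrian non-cases have mean 0:

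- Austria: sensitivity Φ(1.683 − c), specificity Φ(c)
- Netherlands: sensitivity Φ(1.683 − s − c), specificity Φ(c + s)

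| Assumed shift s | c | Netherlands sens/spec | Austria sens/spec |
|---|---|---|---|
| 0 | 0.842 | 0.80/0.80 | 0.80/0.80 |
| 0.25 SD | 0.765 | 0.75/0.84 | 0.82/0.78 |
| 0.5 SD | 0.690 | 0.69/0.88 | 0.84/0.76 |

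Most of the effect is an exchange of sensitivity for specificity. If the shift ran the other way, the exchange would reverse.

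**5. What can 100 patients show by country?** Wilson 95% intervals, with the same stand-in for cases and non-cases:

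- Netherlands: sensitivity 16/20 = 0.80, interval 0.58–0.92; specificity 8/10 = 0.80, interval 0.49–0.94
- Austria: sensitivity 40/50 = 0.80, interval 0.67–0.89; specificity 16/20 = 0.80, interval 0.58–0.92

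The between-country AUC difference detectable with 80% power at an AUC of 0.80 is about 0.27 (Hanley–McNeil standard errors). Per-country figures can be descriptive only.

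**The case against.** The strongest objection is that the analysis section is a short summary in a journal article. Centre covariates and subgroup checks are commonly left to the full protocol or analysis plan, which is not shown, and nothing in the article excludes them. The regression variables it lists are those whose relationship is studied, not a closed covariate set. This stands. A reader might infer that the trial will ignore country; the article does not say so. The point is therefore a recommendation tied to the stated sampling design, not a charge of missing text.

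A reader might also infer that the quotas bias the high-versus-low comparison. Step 2 shows that they do not to any material degree. That near-balance is imposed by design, however, so it says nothing about whether scores mean the same in both countries.

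A third inference would be that the German and Dutch versions score differently, or that the English version is claimed as validated without data. No figure in the article supports or refutes a difference between versions. It makes no separate claim for the English form, and the languages used in phase 2 can only be inferred from the location of the sites.

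Finally, centre differences are partly controlled: one ophthalmologist grades all fundus images, lens opacity has a named grading scale, and many tests have common stated thresholds. This narrows the concern but does not reach questionnaire language, reading speed or the choice of perimeter.

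**Conclusion.** The point holds as a minor one. The sample is stratified by country, country coincides with the examining team and probably with language, and the named analyses carry no country term. Pooled associations and the pooled cut-off can therefore absorb between-centre differences.

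The size is unknown, because the article gives nothing from which to estimate such differences. Under assumed shifts of 0.25 to 0.5 SD, sensitivity at a pooled cut-off would differ between countries by about 0.07 (0.82 − 0.75) to 0.15 (0.84 − 0.69). Country alone would induce a correlation of 0.05 to 0.17 only if both measures differed by 0.5 to 1 SD between centres. These are illustrations, not estimates. There is no numerical error in the plan, and the documents do not support a finding of bias.

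**What to change.** 1. Add country as a covariate in the objective 3 multiple linear regressions.
2. Keep one pooled ROC cut-off per domain and for the total score, and report its sensitivity and specificity by country with 95% confidence intervals, labelled as descriptive.
3. State which language versions the phase 2 patients completed, and limit the validation conclusion to those versions.

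Separate ROC or agreement analyses within each country are not advised, because the Dutch cells (20 high, 10 low) are too small to guide a decision.

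The cost is one degree of freedom in each regression and a small additional table. The Dutch intervals will be wide and should not be read as evidence that the versions are equivalent. No new data are needed for country, which is known for every patient.

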#### Procedures and assessments

All assessments will be performed during regular medication use, preferably in an “ON-state”. The assessment will start with obtaining demographics and medical history. The neurological and ophthalmological assessments consist of an extensive test battery (Table 3).

**Table 3 Tab3:** List of assessments

Outcome	Ophthalmological Assessment
	*Subjective ophthalmological assessment*
Visual acuity	ETDRS logMAR
Reading speed, near visual acuity	Radner Reading Chart
Visual fields	Humphrey field analyser 30–2, Amsler grid
Contrast vision	Low-contrast letter charts (Pelli-Robson),
Colour vision	Ishihara plates/Farnsworth Munsell hue test (desaturated 15D)
Ocular motility	Eye follow movements, Cover test 30 cm and 6 m, Prism test (15 diopter), Eye-Tracking
Facial emotion recognition	Emotion Recognition Inventory (ERI)
Visual function	VFQ-25, Visual impairment screening questionnaire
	*Objective ophthalmological assessment*
Lens opacity	Slit lamp examination
Fundus appearance	Color Fundusphotography (7-fields)
Corneal thickness	Pachymetry
Intraocular pressure	(Goldmann) tonometry
Tear production	Schirmer’s test, TearFilmBreakUpTime, eye blink rate
Anatomical changes of the retina including thickness	Spectral-domain OCT (Heidelberg)
Retinal micro vascular changes	Angio-OCT (Heidelberg)
Outcome	Neurological assessment
PD-related disability and impairment	MDS-UPDRS, Schwab & England activities of Daily living, NMSS, PDQ-39.
Gait and Balance	Timed Up and Go test, Single Leg Stance test, Gait Speed (4 m walking), Dual tasking, Freezing of Gait, Tandem gait
Hand-eye coordination	9 Hole Pegboard test
Cognitive function	MoCA, CLOX
Mood	GDS

List of study protocol assessments, divided in ophthalmological and neurological assessment

Abbreviations: *EDTRS* Early Treatment of Diabetic Retinopathy Study, *D* diopter, *OCT* optical coherence tomography, *NMSS* non-motor symptoms assessment scale, *PDQ-39* Parkinson’s Disease Questionnaire, MoCA [47], Montreal Cognitive Assessment, CLOX, clock drawing test [48], GDS, Geriatric depression scale [49], VFQ-25, visual functioquestionnaire [72, 73]

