**Methods:**

This study consists of two phases. In phase one, 750 PD patients and 250 healthy controls will be recruited to complete the VIPD-Q. In phase two, a subgroup of responders (*n* = 100) (with the highest and lowest scores on the VIPD-Q) will be invited for an extensive neurological and ophthalmological assessment. The in-depth ophthalmologic examination will serve as the “gold standard” for validating the VIPD-Q. Moreover, these assessments will be used to study associations between visual disorders and clinical presentation, in order to gain more insight in their clinical impact.

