#### Neurological examination

PD symptoms and severity including non-motor symptoms will be measured using the Movement Disorders Society Unified Parkinson’s disease Rating Scale (MDS-UPDRS) [35]. The non-motor symptoms scale (NMSS) [36] and the Parkinson’s disease questionnaire-39 (PDQ-39- quality of life) [37] will be used to assess the full spectrum of PD symptoms. Hand-eye coordination and manual dexterity will be tested using the nine-hole peg test [38]. Mood and cognition will be assessed by the Montreal cognitive assessment (MoCA), the CLOX II test and the geriatric depression scale (GDS).

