### Ophthalmological assessment

#### Subjective assessment

Some of the ophthalmological assessments require responses from the patient and are therefore defined as subjective measurements. The outcomes are visual acuity, visual field testing, contrast sensitivity, colour vision, ocular motility, facial emotion recognition and the visual function questionnaire (VFQ-25) concerning visual function. We start the assessment with measuring the best corrected visual acuity at distance, by using the Early Treatment of Diabetic Retinopathy Study (ETDRS) chart at 6 m [47]. 20/30–20/60 is considered mild vision loss, or near-normal vision, 20/70–20/160, moderate visual impairment and 20/200–20/400 severe visual impairment. This is followed by testing reading or near visual acuity, tested with the Radner reading charts at 40 cm distance [48]. Reading correction is applied if applicable. The reading speed is scored in words per minute. Possible visual fields deficits including problems in the peripheral vision are tested with the Humphrey or Octopus Automated Field Analyzer in a standardized design (SITA STANDARD 30–2) and analyzed by an ophthalmologist [49]. To measure the ability to detect objects at low contrast, we will measure the contrast sensitivity with the Pelli-Robson charts. This assessment consists of letters arranged in groups with varying contrast, from high to low. Scores are based on the contrast of the last group in which two or three letters were correctly read, this can be calculated in a logarithmic contrast sensitivity score (CSS). In an elderly population (above 60 years old) a CSS lower than 1.50 is considered as decreased contrast sensitivity in [50]. Colour discrimination is the ability to distinguish differences between shades of colours and is divided in primary colours (green, red, blue and yellow) and their axis (red-green, blue-yellow). To evaluate colour vision pseudo-isochromatic plates with coloured dots forming numbers (Ishihara plates) will be used as a screening tool. As a second step the Farnsworth desatured 15D hue test will be performed to evaluate more subtle colour vision deficiencies. This task consists of ordering 15 coloured caps over trays in an incremental manner according to their hue. Colour vision deficiency will be scored in type of colour deficiency and in severity [51, 52].

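### The regression of visual problems on gait and clinical measures names no cognitive score, although MoCA is collected and only dementia is excluded

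*Protocol article*

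**What the plan says.** All places are in the protocol article.

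- **Eye tests.** Table 3 (Procedures and assessments) divides the eye battery into two blocks, the first headed "Subjective ophthalmological assessment". The section Subjective assessment gives the reason: "Some of the ophthalmological assessments require responses from the patient and are therefore defined as subjective measurements". The block holds acuity, reading, visual fields, contrast, colour, motility, emotion recognition and visual-function questionnaires. On reading it adds: "The reading speed is scored in words per minute".
- **Cognition.** The section Neurological examination states: "Mood and cognition will be assessed by the Montreal cognitive assessment (MoCA), the CLOX II test and the geriatric depression scale (GDS". Table 2 lists "Dementia according to DSM-IV" as an exclusion and sets no MoCA limit. The Background names cognitive decline among the non-motor symptoms of PD.
- **Gait.** The section Gait and balance tests walking both alone and with a second task.
- **Regression.** The last paragraph of the Statistical analysis plan names the variables of a multiple linear regression: falls, disease duration, MDS-UPDRS, hand-eye dexterity, gait and balance tests, and visual problems. Neither MoCA nor CLOX is among them.
- **Validation.** In the same section, "we will compare the results of the VIPD-Q with the ophthalmological assessments using analysis of intraclass correlation coefficient (ICC), with Cohen’s kappa", and "The results of the ophthalmological assessments will be categorized in visual disorders within the domains of the VIPD-Q".

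**The concern.** The third objective is the impact of eye disorders on clinical functioning, with gait and balance singled out. In that analysis visual problems are the exposure. If they are scored from tests on which the patient must attend, respond and follow instructions, part of the score may reflect cognition rather than the eye. Gait may depend on cognition too, most plausibly under dual-tasking. Cognition is then a plausible common cause of both sides of the regression. It is measured in phase 2, but it is not in the named list.

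At stake is the reading of the result. A vision-gait association could be reported as a consequence of eye disease, and as a reason to expect better mobility from eye treatment, when part or all of it is cognitive.

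**Working it through.** The plan gives no power calculation, effect size or correlation for this analysis, so there is no stated figure to reproduce. What follows is an illustration on assumed correlations.

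**Inputs**
- n = 100, the phase 2 sample (Patient collective and recruitment).
- Two-sided 5% test: assumed, as the article states no level for this analysis.
- Correlation a of cognition with the vision score and b with gait: assumed equal, central value 0.3, range 0.2 to 0.4.
- No true effect of vision on gait, and no other covariates.

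**Step 1: induced correlation.** If vision and gait are linked only through cognition, their unadjusted correlation is r = a × b.

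**Step 2: rejection rate by Fisher's z.** m = atanh(r) × √(n − 3) = atanh(r) × √97. The rate is Φ(m − 1.96) + Φ(−m − 1.96).

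| a = b | r | m | Rejection rate |
|---|---|---|---|
| 0.2 | 0.04 | 0.394 | 0.059 + 0.009 = 6.8% |
| 0.3 | 0.09 | 0.889 | 0.142 + 0.002 = 14.4% |
| 0.4 | 0.16 | 1.590 | 0.3555 + 0.0002 = 35.6% |

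A least-squares simulation (4,000 runs) at a = b = 0.3 gave 14.5% without cognition in the model and 5.3% with it.

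**Step 3: the dementia exclusion.** Excluding dementia narrows the spread of cognition. If it cuts the SD to u = 0.7 of its unrestricted value (assumed), each correlation becomes a·u / √(1 − a² + a²u²).
- a = 0.3: 0.21 / √0.9541 = 0.215; r = 0.215² = 0.046; rate 7.4%.
- a = 0.4: 0.28 / √0.9184 = 0.292; r = 0.085; rate 13.4%.

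**Step 4: MDS-UPDRS as a partial stand-in.** Suppose MDS-UPDRS correlates 0.5 with cognition (assumed), and with vision and gait only through cognition. At a = 0.3 its correlation with each is 0.5 × 0.3 = 0.15. The vision-gait correlation given MDS-UPDRS is (0.09 − 0.15²) / (1 − 0.15²) = 0.0675 / 0.9775 = 0.069. With one covariate, m = atanh(0.069) × √96 = 0.68, and the rate is about 10%. By the same formula the rate is about 6% at a = 0.2 and 23% at a = 0.4.

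Each safeguard lowers the excess. Under these assumptions neither removes it at correlations of 0.3 or 0.4.

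**The case against.** **The list may be incomplete.** The article condenses a fuller plan. Its regression sentence does not say which variables are outcomes, exposures or covariates, and age and sex are absent too. An unseen plan may add cognition. This stands as a limit. The article does, however, name its variables and includes two measures of disease stage and severity; on that stated list, a collected and plausible confounder is missing.

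**MDS-UPDRS may already carry cognition.** The section Neurological examination says that this scale covers non-motor symptoms. So it would be too strong to say that cognition is wholly absent from the model. Part may be adjusted for; nothing shows that all of it is.

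**Visual problems are not tied to particular tests.** If they were scored from objective findings alone, this route to bias would largely close. The concern is conditional on that definition.

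**Slowing is only part of the battery.** Reading is the only response-dependent eye test for which the article gives a speed score. The documents do not show how far mild impairment lowers the other results.

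**Adjustment can overcorrect.** CLOX is a clock-drawing test, and poor vision can lower a cognitive score. Adjusting may then remove some genuine visual effect. This stands, and is why both estimates should be shown.

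**The validation.** A reader might infer that cognitively impaired patients with healthy eyes will be counted as diseased by the reference, so that the cut-offs partly measure cognition. The abstract does say that the "ophthalmologic examination will serve as the “gold standard” for validating the VIPD-Q", and no cognitive term enters that analysis. But the article does not say which tests make a domain positive. Many diagnoses in Table 1 rest on slit lamp, fundus, tear tests or an orthoptist's examination, and an ophthalmologist analyses the fields. The documents do not support that inference.

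**Conclusion.** The point holds for the vision-gait regression, as a recommended change rather than an essential one. A measured and plausible common cause is missing from the variables that the article names, and dementia as the sole cognitive exclusion leaves milder impairment in the sample.

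The size cannot be fixed from the documents. The range of about 7% to 36% for a nominal 5% test (14% at the central value) rests on assumed correlations, no true link, 100 patients and no other covariates. It is an upper illustration to the extent that MDS-UPDRS or the dementia exclusion absorbs part of the effect; at the lower end the excess over 5% is small.

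For the questionnaire validation, no error is established. A reader might go further and want the conclusions based on objective tests alone. That would drop fields, colour, contrast and acuity, although the Background counts field deficits and reduced colour and contrast vision as visual problems, and Table 1 includes refraction errors. It would narrow what the study sets out to measure.

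**What to change.** Add MoCA as a covariate in the vision-gait regression. Report the coefficient for visual problems with and without it, side by side, and attribute an association to vision only if it persists after adjustment. If it shrinks materially, say that cognition and over-adjustment are both possible explanations.

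The data are already in the phase 2 battery, so the cost is one degree of freedom and one extra column of results. The drawback is possible over-adjustment, which the paired estimates make visible.

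Optionally, repeat the domain agreement and cut-offs with a reference built from objective tests, in the domains that have them (ocular surface, intra-ocular, optic nerve); Table 3 lists none for the oculomotor domain. Label this a sensitivity analysis and keep the full reference as the basis for the conclusion.
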